#### Qualitative Data Analysis

We will use 2 different methods of qualitative data collection: focus groups and semistructured individual interviews. The combination of focus groups and individual interviews will make 3 unique contributions: (1) provide an iterative process whereby an initial model of the phenomenon is guided by the description and exploration of individual accounts; (2) identify sensitive cultural, environmental, and contextual circumstances through individual interviews, adding interpretation of the phenomenon; and (3) allow for central and common characteristics to be further explored across focus groups with members who share similarities [68]. In qualitative research, data collection and analysis occur simultaneously. Analysis of interview data proceeds inductively through the identification of recurring themes and patterns in transcripts, field notes, and analytic memos. A thematic analysis framework will be used in this study. The thematic analysis allows researchers to highlight the similarities and differences across groups of participants [61]. The research staff will work from an essentialist or realist perspective that assumes that the participant’s language reflects their experiences, meanings, and realities. Meaningful analytical units will then be developed using a coding scheme informed by the dominant themes in the data. Topics will then be divided into several subtopics based on recurring themes within the larger topics, allowing a more in-depth analysis and complex understanding and interpretation of each particular theme. Each theme and subtheme will be assigned a code, and the codes will be compiled in a codebook. All interviews will be conducted by the research staff. As analysis is taking place, questions for individual interviews will be developed as focus group data are being analyzed. Individual interview data will be analyzed using the same steps used for the focus group data. We hypothesize significant differences in the experiences and perceptions of youth in the study based on their age, race, gender, and socioeconomic status.

#### Strategies for Trustworthiness

Members of the research team will have prolonged engagement within the community to gain a better understanding of the organization in which participants were recruited from and to establish trust with participants. A confirmability audit will be conducted, where multiple coders will be used to analyze the data. The process will be the same for both the individual interviews and focus groups. Data from the interviews will first be analyzed by interviewers using open coding, whereby concepts are identified and labeled as they emerge from the data and across the interviews. Interviews will be transcribed and analyzed using NVivo 12 (QSR International) software [71]. The coding process will be inductive in nature and consist of categorization and grouping. Line-by-line coding will be used, and common themes will be grouped together using a coding map created from NVivo to conceptualize the themes until 4 main categories are identified. At least 90% interrater reliability will be achieved before the codes and categories are developed. The categories that will be developed from the coding process will not be predetermined but rather formed during the coding process. After the initial coding of the data, the research team will summarize and organize the results in NVivo [71].

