#### Qualitative Data Collection

First, participants will be asked to complete a 60- to 90-minute focus group with a trained facilitator. Focus group methodology provides insight and understanding of the phenomena by allowing the researcher to examine interactions among participants [60]. Focus groups will be stratified by age (eg, 12-13, 14-15, 16-18, and 19-21 years), gender (eg, male, female, and transgender), and race (eg, Black, Hispanic, and Bangladeshi). We hypothesize significant differences in risk and protective factors for substance abuse and mental health by group. Each focus group will comprise 5-8 youth participants. Although previous research indicated that 3 focus groups can yield saturation [61], we anticipate conducting 12 focus groups to improve study rigor and account for saturation within each subgroup of youth. For each focus group, 2 facilitators will be involved. Facilitators will be closely matched to youth participants by race, ethnicity, and gender. Following the focus groups, a subsample of (N=50) youth will be asked to participate in individual interviews to triangulate the data and delve deeper into sensitive themes that arose in focus groups. The lead facilitator will also interview the participants individually. The second cofacilitator will take notes of observations of nonverbal exchanges, including displays of emotion and nervous gestures that took place during the interviews. Adaptive questions will be used to further understand the unique experiences that youths are sharing. All interviews will be recorded and transcribed. As the interview process develops, questions may be tailored based on the youths’ feedback. The youth and community advisory board will review, revise, and approve the focus group and individual interview questions. Participants will receive US $25 at the end of the focus group interview and US $25 at the end of individual interviews.

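### Grouping of qualitative themes is set to end at four main categories, an unexplained number fixed before data collection, although the same section calls coding inductive and says categories are not predetermined

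*Protocol article*

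**What the plan says.** Strategies for Trustworthiness describes open, line-by-line coding in NVivo, after which common themes are grouped with a coding map to "conceptualize the themes until 4 main categories are identified". The same paragraph says: "The coding process will be inductive in nature and consist of categorization and grouping." Two sentences after the number four comes: "The categories that will be developed from the coding process will not be predetermined but rather formed during the coding process."

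Qualitative Data Analysis sets the same inductive approach: "Analysis of interview data proceeds inductively through the identification of recurring themes and patterns in transcripts, field notes, and analytic memos." Below the top level it fixes no count: "Topics will then be divided into several subtopics based on recurring themes within the larger topics." It also expects experiences and perceptions to differ by age, race, gender and socioeconomic status.

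Saturation is mentioned only under Qualitative Data Collection, as a reason for the planned number of groups: "we anticipate conducting 12 focus groups to improve study rigor and account for saturation within each subgroup of youth."

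**The concern.** In an inductive thematic analysis, the number of top-level categories is something the data show. Here it is stated in advance, and the word that introduces it makes it the end point of the grouping step. The same paragraph says the categories are left to emerge. An analyst following the text cannot fully honour both statements: either grouping continues until the count is four, or the structure is allowed to form from the data.

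The qualitative findings have a later use. The Discussion (Principal Findings) says data from this phase will guide the selection and adaptation of a prevention intervention, with gender, race and developmental differences taken into account and possibly more than one adaptation. If the top-level structure is shaped by a preset count, content specific to a smaller subgroup may end up beneath a broader heading and receive less attention at that stage.

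**Working it through.** No arithmetic applies. The four is a stated rule and is not derived from any input, so there is no figure to reproduce. The check is a comparison of the relevant sections.

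1. **When the number is fixed.** The Results overview says the study is in its first planning phase and that recruitment begins at the end of year 1 (August 2021). The four therefore cannot have come from this study's data.

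2. **What the number governs.** The clause attaches to the grouping of themes into main categories. It is not attached to open coding, line-by-line coding, focus groups or interviews. It is a rule about the top level of the structure only.

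3. **Whether the number is justified elsewhere.** Qualitative Interview Outcomes lists three research questions, which does not give four. Qualitative Data Analysis names four characteristics on which differences are expected (age, race, gender, socioeconomic status), but the article does not link the category count to them, and characteristics of participants are not thematic categories. No section gives a reason.

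4. **What the same section says against it.** Coding is inductive, and the categories "will not be predetermined but rather formed during the coding process". Taken at face value, this excludes a number set beforehand.

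5. **What follows if the rule is applied.** Let k be the number of main categories that the coded data support.
   - If k is greater than 4, at least k − 4 mergers are needed. With k = 6, for example, that is 2.
   - If k is less than 4, at least 4 − k splits are needed. With k = 3, that is 1.
   - Only if k equals 4 does the rule change nothing.

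   The values of k are illustrations. The document gives no basis for predicting k.

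6. **What is not affected.** Qualitative Data Analysis leaves the number of subtopics open and gives every theme and subtheme a code. A theme that does not form its own main category can be kept at a lower level. The 12 focus groups and 50 individual interviews are set under Qualitative Interview Outcomes and Qualitative Data Collection, and nothing in the grouping rule shortens them.

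**The case against.** The strongest defence is that the two statements concern different things: the content of the categories is open, while four is an intended level of aggregation. Placing themes under a few broad headings is what grouping means, and how many headings to use is partly a matter of taste. The article is also condensed, and a codebook is planned.

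Part of this stands. The reading is possible, and it makes the conflict less stark. But the article does not say it, and even on that reading the number of main categories is a predetermined feature of a structure described as formed during coding. Nor does the point rest on missing detail, because the article itself states the number.

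Three stronger inferences are tempting, and the document does not support them.

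- **Coding stops, or the total number of themes is fixed, at four.** Only main categories are numbered. Coding and the lower levels are not capped.
- **Further themes are dropped, so subgroup content is lost.** No section says a theme is discarded. Extra themes can sit under a main category, and Qualitative Data Analysis expects similarities and differences across groups to be highlighted. Such content may be submerged; it is not necessarily removed.
- **The rule overrides the plan to "account for saturation within each subgroup of youth".** That phrase justifies the number of focus groups, which is data collection. The rule of four governs how collected data are organised and ends no data collection early.

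**Conclusion.** The point holds in a limited form. One section fixes the number of main categories before any data exist, gives no reason, and says that categories are not predetermined. If the rule is followed literally, the top-level structure is partly a product of the rule whenever the data support a number other than four.

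The conclusion assumes that the clause is meant as an end point, which is its ordinary reading, and that the top-level categories will carry weight when interventions are adapted, which the Discussion suggests but does not spell out. The size of any effect on content cannot be estimated from the document. No sample size, power figure or quantitative analysis depends on it. The correction is worth making because the inconsistency is plain and cheap to remove.

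**What to change.** In Strategies for Trustworthiness, delete the number 4. State that grouping ends when the coded themes are accounted for and further review yields no new main category, and that the number of main categories will be reported as a result. The sentence saying that categories are not predetermined can then stand unchanged.

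Leave the planned 12 focus groups and 50 interviews as they are. A saturation rule applied within each stratum would be the wrong repair. It would govern data collection instead of grouping, and it does not fit the plan: the example strata of four age bands, three genders and three race groups cross to 4 × 3 × 3 = 36 cells, against 12 groups.

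The cost is a change of wording, best made before coding starts. The downside is that the length of the coding phase becomes slightly less predictable.

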#### Integration

The analysis of quantitative and qualitative data will initially be conducted separately. Subsequently, we will merge all sets of findings. Member checking of the data will occur in townhalls and disseminating findings throughout the community in the form of infographics and educational materials. The aim of this approach is to balance the respective strengths and weaknesses of each method to maximize the yield of distinct complementary sources of evidence. The main statistical software package that will be used for this project to analyze data and to evaluate the project as well as analyze survey data will be SAS version 9.4 [72], and NVivo will be used to analyze qualitative findings [71].

## Discussion

### Principal Findings

Researchers have struggled with ways to achieve community-based samples that are representative and include an adequate number of youths. In addition, understanding what prevention methods work with youth who are most in need of substance abuse and mental health prevention services, such as street-involved and truant youth, is crucial, and their input is essential, yet their voices are often ignored because of the challenges in reaching this population. Such an absence may make it difficult for interventions to be truly effective for this population. This study proposes innovative methods such as venue-based sampling to recruit and engage with a hard-to-reach population in Paterson, New Jersey. Few studies have used venue-based sampling in youth studies; however, those that have, offered beneficial results through recruitment of hard-to-reach youth [52,73]. A majority of youths are recruited from schools; however, this can lead to bias and neglect of youth who are truant or not connected to youth-serving organizations. Venue-based sampling has the advantage of allowing a comprehensive focus on a single, entire community that can be translated into an effective, culturally tailored, community-based intervention. Venue-based sampling also allows research teams to be fully immersed in the community as an outreach. Through this method, we intend to recruit participants to be a part of our study for data collection and also simultaneously connect youth to our youth-serving community partners. Through this approach, youth become connected to organizations that can serve their needs while contributing their knowledge and experiences as experts of their lived realities to prevention science.

In the final phase of the study, we will use the data to design and iteratively adapt an evidence-based substance abuse and mental health prevention intervention accounting for gender, race, and developmental differences. As we anticipate significant differences across subgroups of Paterson youth, the adaptation of multiple interventions will be expected to fit their diverse needs and experiences. The process of modifying an evidence-based intervention without contradicting its core elements or internal logic is referred to as *adaptation*. Without attention to the cultural context of a new target population, adapted interventions may remain faithful to the underlying theoretical framework and core elements on which they were originally developed but, unfortunately, may lack relevance, sustainability, and acceptability for the target population [29]. Therefore, to effectively implement a successful evidence-based intervention, this study will use assessment, decision, administration, production, topical experts, integration, training, and testing (ADAPT-ITT) [74], a well-known implementation science framework. The framework specifies 8 steps for adapting interventions to new priorities. The first step involves the assessment of service users’ needs, which guides decision making about the modifications that are needed (step 2). The third step involves intervention adaptation and initial administration of the program to potential service users to identify where the intervention requires revision to improve its relevance and acceptability. Thereafter, intervention production occurs in which further adaptations are made (step 4), and this revised intervention is reviewed by topical experts (step 5). Steps 6 to 8 involve integrating all feedback into a final version of the intervention, training staff to deliver the intervention, and feasibility testing of the intervention. The youth and community advisory board and research team will be involved in the adaptation of evidence-based interventions for Paterson youth. As we hypothesize that significant differences will arise in risk and protective factors for youth throughout Paterson, we anticipate adapting a session-based prevention intervention that is structured, informative, and engaging in youths of all ages. Although there are a number of community-based prevention interventions that are geared toward substance use and mental health among urban youth, pending initial data collection and community input, we anticipate adapting the CASASTART (Center on Addiction and Substance Abuse Striving Together to Achieve Rewarding Tomorrows) [75] and Project Towards No Drug Abuse [76].

CASASTART [75] has been identified as a model substance abuse prevention program. CASASTART was originally developed as a substance abuse and violence prevention program serving high-risk adolescents and their families living in socially distressed neighborhoods [75]. The program is a comprehensive, neighborhood-based, school-centered model that aims to provide coordination among police, schools, and community-based organizations to achieve 3 goals: (1) to redirect and build resiliency in the lives of youth who are at risk of using drugs, becoming delinquent, or dropping out of school; (2) to reduce and control illegal drug use and related crime in the neighborhoods where youth live to make the areas safer and the environment more nurturing; and (3) to connect youth and their families to services critical to their well-being in the environment [75]. Another community-based prevention intervention for youth is the Project Towards No Drug Abuse [76] program, which is a 12-session curriculum for youth that targets substance use and violence-related behaviors through the use of a motivation, skills, and decision-making approach. Using interactive teaching techniques, Project Towards No Drug Abuse provides cognitive motivation enhancement activities, information about the consequences of drug use, correction of cognitive misperceptions, communication and coping skills enhancement, and tobacco cessation techniques to students. Although both of these model interventions have shown efficacy in improving knowledge, reducing risky behaviors, and improving mental health outcomes; these interventions often do not reach the most vulnerable youth who are in need of such services as such interventions are performed in school settings [12]. Reaching the most vulnerable youth who may not be connected to schools or organizations or are street-involved is key to effectively addressing youth substance use and mental health as their input on barriers to prevention and treatment are vital to intervention development. Given the knowledge that researchers have on prevention interventions for youth, community-based and culturally relevant interventions are the gold standard for urban communities [77]. It is essential that researchers aim to work with communities on developing solutions that are innovative, specific to their needs, incorporate community members, and reach a wide array of youth who may have various risk factors that need to be addressed in prevention intervention initiatives.

According to the prevention principles proposed by the National Institute on Drug Abuse [78], “Community prevention programs that combine two or more effective programs can be more effective than a single program alone.” Building on these guiding principles, we aim to adopt a comprehensive substance abuse prevention approach that includes mental health education and resource connecting through intensive case management, community mobilization, and interactive education-based interventions. On the basis of prior research, this multitiered strategy has proven to be an effective method for reducing substance abuse risk among urban minority youth [78] CASASTART [75], uses a case management approach in which an individual (trained case manager) works with up to 15 children and their families and directly provides or, through appropriate referral, coordinates a comprehensive menu of services for the youth and their families. The model recommends that each community should implement the intervention and develop its own approach to design and deliver services consistent with local culture and practice. Within this model and with youth and community advisory board approval, we will have a research assistant trained in social work or counseling, provide services that specifically include referring youth to nearby mental health clinics, mentoring programs, and extracurricular activities to keep youth engaged. The case manager will perform a biweekly follow-up with participants to ensure that they are supported and engaged in recommended activities.

The Project Towards No Drug Abuse [76] is a 12-session curriculum that targets substance use and violence-related behaviors through the use of motivation, skills, and decision-making approaches. The curriculum comprises 12 sessions, approximately 45 minutes each, which are designed to be implemented over a 4-week period. Using interactive teaching techniques, the instruction to participants provides cognitive motivation enhancement activities, information about the consequences of drug use, correction of cognitive misperceptions, communication and coping skills enhancement, and tobacco cessation techniques. Although this intervention was originally intended to be implemented in alternative schools, it also provides flexibility to be adapted for youth who are not in school [76]. We have the commitment of community partners with large access to youth both in school and outside of school, which will provide us with space within the community to pilot-test the intervention.

The last phase of the project includes a pilot feasibility trial of the adapted intervention among a sample of youth living in Paterson, New Jersey. During monthly meetings with youth and community advisory board members, research staff will discuss the use of evidence-based prevention interventions that address youth substance use and mental health. A specific strategy and an evidence-based intervention (eg, Substance Abuse and Mental Health Services Administration’s National Registry of Evidence-based Programs and Practices) will be decided through findings collected from venue-based sampling methods and suggestions from the youth and community advisory board. Participants will be recruited from partnering youth organizations to participate in the intervention. We will pilot-test the intervention with a group of youths who are similar developmentally by age, race, ethnicity, and gender. Youth will be sampled from schools and youth-serving organizations across all 6 wards. Although interventions have the power to increase perception, increase knowledge about substances, and reduce risky behaviors, we understand that youth are nested in their environments. Therefore, we are cautious of being ambitious in our goals, as changes cannot occur if the community norms remain the same. Consequently, we will meet the youth and community advisory board to decipher the most effective mode of intervention that can occur at the individual and community levels. We intend to pilot a combination of effective strategies (eg, prevention education, case management, and referral to therapy). We will first identify and adapt an evidence-based intervention that will incorporate elements of mental health discussions, substance use, and refusal strategies, as these have proven to be the most effective among ethnic minority youth. In addition, and most importantly, the intervention will be informed by findings from participants and youth and community advisory board discussions. Although we discussed earlier the flaws in primarily recruiting and working with youth in schools only, the priority will be to adapt an existing prevention intervention to be feasible for youth who are in school and other youth who are not engaged in school. We hypothesize that unique developmental, cultural, racial, and gender-specific differences will arise and inform how to adequately decide, adapt, and deliver an effective prevention intervention for Paterson youth.

